### Exclusion criteria

The patient’s condition in the critical or acute stage is unstableThose with deafness, aphasia or severe cognitive impairment who find communicate difficult normallyPatients with psychiatric diseases, malignant tumors, severe bleeding tendency and infections of the treatment sitesSystolic blood pressure is more than 180 mmHg or diastolic blood pressure is more than 110 mmHgParticipating in other clinical trials or studies within 3 months and receiving other related treatments in the middle of the study may affect the judgment of the efficacy of this studyDysfunction of muscle tone caused by other causes and previous motor dysfunctionPregnant and lactating womenFear of needling, fainting with needles, etc.

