### Sample size

Our study will be designed as a randomized controlled trial, and the main outcome is whether hand spasm after stroke is relieved after treatment. Current experience shows that the previous effectiveness rate of conventional acupuncture treatment is about 50%, and the expected effectiveness rate is 85%. The significance test level is 0.05, and the test power is 0.9. Sample size is calculated by using:

$$ \mathit{\mathsf{N}}={\left(\mathit{\mathsf{U}\mathsf{\alpha }}+\mathit{\mathsf{U}\mathsf{\beta }}\right)}^{\mathsf{2}}\times \mathsf{2P}\left(\mathsf{1}-\mathit{\mathsf{P}}\right)/{\left(\mathit{\mathsf{P}\mathsf{1}}-\mathit{\mathsf{P}\mathsf{0}}\right)}^{\mathsf{2}}, $$

where, *N* is the required sample size for each treatment group, and the sample size of each group is equal. When *α* is 0.05 and *β* is 0.1, the normal distribution quantile table shows that:
$$ \mathit{\mathsf{U}\mathsf{\alpha }}\left(\mathsf{0.05}\right)=\mathsf{1.65},\mathsf{and} $$
$$ \mathit{\mathsf{U}\mathsf{\beta }}\left(\mathsf{0.1}\right)=\mathsf{1.28}. $$

*P0* and *P1* represent the original curative effect and the expected curative effect, 50% and 85%, respectively. By substituting the above parameters and values into the formulas, 63 cases will be needed for each group. Accounting for a 10% expulsion rate, the final estimated sample size will be about 70 cases per group (210 in total).

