### Inclusion criteria

Cerebral hemorrhage or cerebral infarction confirmed by computed tomography (CT) or magnetic resonance imaging (MRI)First onset, unilateral hemiplegiaThe onset time is more than 2 weeks, and the vital signs are stableAge 30–80 yearsThe clinical manifestations are spastic paralysis of the upper limbs, Brunnstrom stages II–IV of the upper limbs and hands with hemiplegiaThe improved Ashworth score of the hand of the hemiplegic side is grade 1^+^ to 3Stable condition, clear consciousness, no aphasia, no intellectual impairment, can understand the content of the scale and cooperate with the examination and treatmentNo sedative or muscle relaxant has been taken in the last 2 weeksPatients have signed an informed consent form

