### Elimination criteria

Patients who have been mistakenly admitted or misdiagnosedNo intervention is given to the patients after admission

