### Recruitment

Recruitment of patients began on 1 June 2019 and will be completed in June 2021, or after the required number is obtained, whichever is earlier. We will develop plans and methods to contact subjects, including the preparation of informed consent, obtaining necessary data, videos and pictures to help subjects understand the purpose and program of the trial. We will also explain to the subjects the advantages and disadvantages of the treatment and the relevant safety measures to be taken during the trial. In addition, we will post recruitment posters in and around the hospital, or use the Internet for recruitment. According to the inclusion/exclusion criteria, the research team will preliminarily judge the possibility of each subject’s inclusion, and conduct the relevant examination on them after they have signed the informed consent, and finally confirm whether the subjects actually meet the inclusion/exclusion criteria according to the examination results.

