### Randomization

After signing the informed consent, participants will be randomly divided into three groups: an acupuncture group, a sham acupuncture group and a control group. Randomization will be accomplished by qualified researchers using randomization software to generate random-number sequences. In the process of randomization, allocation should be kept hidden. All patients will be randomly divided into groups in a ratio of 1:1:1. The strips revealing treatment allocation will be placed in sealed opaque envelopes with sequential numbers. After obtaining informed consent, the envelopes will be opened in turn. Patients and data analysts are not clear about the randomized grouping.

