#### Case report form

In the trial, the content recorded in the CRF should be consistent with the original material. The CRF must meet the following criteria:
Data must be entered with a black pen and signedIf the participant has received more than 2 weeks of intervention and evaluation, the data of the volunteer should still be recorded and countedIf an error occurs in the record and needs to be corrected, the recorder should draw a horizontal line under the original record, then sign the amendment and indicate the date of correction. Note that it must be ensured that the original record is identifiable after modification.

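### An entry exclusion criterion includes treatment received mid-study, so on its more natural reading a post-randomization event becomes a ground for excluding randomized patients

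*Protocol article*

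**What the plan says.** The disputed item is in the protocol article, Exclusion criteria. It joins participation in other trials to other treatment: "within 3 months and receiving other related treatments in the middle of the study may affect the judgment of the efficacy of this" study.

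The sections around it say the following.

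- **Recruitment.** After consent, patients are examined and the team will "finally confirm whether the subjects actually meet the inclusion/exclusion criteria according to the examination results". The criteria decide entry.
- **Randomization.** "After signing the informed consent, participants will be randomly divided into three groups".
- **Elimination criteria.** This separate, short list begins "Patients who have been mistakenly admitted or" misdiagnosed. Its only other entry is patients who were given no intervention. Co-treatment is not on it.
- **Case report form.** If a "participant has received more than 2 weeks of intervention and evaluation, the data of the volunteer should still be recorded" and counted. Nothing is said about other treatment, or about patients with 2 weeks or less.
- **Sample size.** "Accounting for a 10% expulsion rate, the final estimated sample size will be about 70 cases per group (210 in total"). The grounds for expulsion are not given.
- **Inclusion criteria.** The drug criterion looks clearly backward from entry: no "sedative or muscle relaxant has been taken in the last 2" weeks.

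**The concern.** An entry criterion can use only what is known at entry. Treatment that a patient begins during the study is not known then. If the clause means what it most naturally says, it can only be applied after allocation, to patients who are already randomized.

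That would matter here for three reasons.

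- Patients whose spasm persists are the ones most likely to look for other treatment, and relief of spasm is the outcome on which the sample size rests.
- The chance of starting may differ by arm. Control patients receive no needling, and the Discussion calls blinding of acupuncturists and patients the most challenging aspect of the design.
- Follow-up lasts 6 months after a 4-week intervention, so there is time for other treatment to begin.

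A site that acts on the clause would drop patients for a reason tied to outcome and possibly to arm. A site that reads it as a baseline rule would keep the same patients.

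**Working it through.** **Step 1: timing.** The criteria are confirmed on the screening examination results (Recruitment), and allocation follows consent (Randomization). Mid-study treatment comes after both. Read as a during-study event, the clause cannot do the job of an entry criterion.

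**Step 2: the alternative reading.** The clause speaks of *the* study and then of *this* study. It could mean treatment received within another trial in the past 3 months. That would be an ordinary baseline exclusion and would fit the Recruitment section. The wording allows both readings.

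**Step 3: does another section settle it?** The Elimination criteria do not list co-treatment, which points towards keeping such patients. The Case report form rule also points that way for those past 2 weeks, but it does not say what happens to earlier starters. The 10% allowance in Sample size expects some expulsions without naming grounds. Together these sections lean towards retention but do not rule out acting on the clause.

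**Step 4: illustration of removal.** The article has no figure to reproduce here, and every start rate below is an assumption. Take 70 per arm and 35 relieved in each, so there is no true difference. Assume that starters are not relieved and are removed. The observed rate in an arm with *r* removals is 35/(70 − r).

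- One removal: 35/69 = 50.7%. Seven removals: 35/63 = 55.6%.

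| Removed, control | Removed, acupuncture | Acupuncture minus control |
|---|---|---|
| 10 | 4 | 35/66 − 35/60 = 53.0% − 58.3% = −5.3 points |
| 4 | 10 | 35/60 − 35/66 = +5.3 points |
| 5 | 2 | 35/68 − 35/65 = 51.5% − 53.8% = −2.4 points |
| 2 | 5 | 35/65 − 35/68 = +2.4 points |
| 7 | 7 | 35/63 − 35/63 = 0 |

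If half of the removed patients had been relieved, like the rest of their arm, 10 v 4 removals give 33/66 − 30/60 = 0. Bias needs removal to depend on outcome and to differ by arm.

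**Step 5: cost of keeping starters in.** Assume that 7 of 70 controls start other treatment, that all 7 would otherwise be unrelieved, and that a fraction *f* are relieved by it. The control rate is (35 + 7f)/70. The other arm stays at the 85% planned in Sample size, and the undiluted control rate is the planned 50%.

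Power is for a two-sided 5% test of two proportions with mean rate P = (p0 + p1)/2:

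z = [(p1 − p0) − 1.96·√(2P(1−P)/n)] / √([p0(1−p0) + p1(1−p1)]/n), and power = Φ(z).

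For f = 100% and n = 70: P = 0.725, so z = (0.25 − 1.96 × 0.0755)/0.0725 = 1.41 and power is 92%.

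| f | Control rate | Difference | Power, n = 70 | Power, n = 63 |
|---|---|---|---|---|
| no starters | 50% | 35 points | 99.6% | 99.2% |
| 25% | 36.75/70 = 52.5% | 32.5 points | 99.0% | 98.3% |
| 50% | 38.5/70 = 55% | 30 points | 97.9% | 96.5% |
| 100% | 42/70 = 60% | 25 points | 92.1% | 89.1% |

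With everyone kept, n = 70 is the relevant column. The n = 63 column shows the position if the full 10% allowance is lost for other reasons.

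**The case against.** The strongest reply is structural. Exclusion criteria govern entry, post-entry removal has its own heading, and co-treatment is not under it. A patient who starts other treatment after allocation meets no express removal rule, and the baseline reading is the only one that fits the Recruitment section. Harm needs a site to apply an entry criterion after entry. One hospital coordinates the trial and manages the data, which makes divergent practice less likely. How such patients are analysed is often left to a full protocol or analysis plan that is not shown here.

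Much of this stands. A reader might infer that the protocol orders removal of co-treated patients or contradicts itself. It does neither: no section orders removal, and the passages can be reconciled. A reader might also infer that the clause lacks a time window for prior treatment, in contrast with the 2 weeks set for sedatives and muscle relaxants. That fails on both readings. On the baseline reading the 3 months supply the window, and on the during-study reading prior treatment is not the subject.

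What the reply does not remove is the wording. The point concerns what a stated eligibility criterion says, and eligibility is protocol content. An analysis plan does not decide whom a site excludes. Central coordination does not show which reading the sites were given.

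**Conclusion.** The point holds as a badly worded criterion that leaves the handling of randomized patients ambiguous. On its more natural reading it makes a post-randomization event, possibly dependent on outcome and arm, a ground for exclusion. The baseline reading remains open.

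No bias is demonstrated, and its size and direction are unknown. The shifts of 2.4 and 5.3 points rest wholly on assumed numbers of starters, all unrelieved and all removed. Other assumptions give zero. It would be tempting to conclude that the clause favours acupuncture. The documents do not support that, since the sign reverses with the arm that loses more patients. The change is worth making because it is cheap and protects the randomized comparison.

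**What to change.** Limit the criterion to events before randomization, keep the existing 3-month window for other trials and their treatments, and delete the phrase that places the treatment mid-study. For example: *participation in another clinical trial, or treatment received in one, within 3 months before randomization.*

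Add one sentence: *patients who begin other treatment for spasm after randomization, at whatever time, remain in follow-up with all scheduled assessments and are analysed in their allocated group; the start date is recorded on the CRF.*

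The 2-week window should stay with sedatives and muscle relaxants. Extending it to all antispastic treatment would be a new eligibility rule and could shorten a 3-month exclusion.

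The cost is a wording amendment, one added sentence and one CRF entry, with no extra visits or patients. The statistical price is possible dilution. In the assumed example the 35-point difference falls to between 32.5 and 25 points, and power with all 70 per arm kept stays at about 92% or more (89% at 63 per arm).

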### Elimination criteria

Patients who have been mistakenly admitted or misdiagnosedNo intervention is given to the patients after admission

### Recruitment

Recruitment of patients began on 1 June 2019 and will be completed in June 2021, or after the required number is obtained, whichever is earlier. We will develop plans and methods to contact subjects, including the preparation of informed consent, obtaining necessary data, videos and pictures to help subjects understand the purpose and program of the trial. We will also explain to the subjects the advantages and disadvantages of the treatment and the relevant safety measures to be taken during the trial. In addition, we will post recruitment posters in and around the hospital, or use the Internet for recruitment. According to the inclusion/exclusion criteria, the research team will preliminarily judge the possibility of each subject’s inclusion, and conduct the relevant examination on them after they have signed the informed consent, and finally confirm whether the subjects actually meet the inclusion/exclusion criteria according to the examination results.

### Randomization

After signing the informed consent, participants will be randomly divided into three groups: an acupuncture group, a sham acupuncture group and a control group. Randomization will be accomplished by qualified researchers using randomization software to generate random-number sequences. In the process of randomization, allocation should be kept hidden. All patients will be randomly divided into groups in a ratio of 1:1:1. The strips revealing treatment allocation will be placed in sealed opaque envelopes with sequential numbers. After obtaining informed consent, the envelopes will be opened in turn. Patients and data analysts are not clear about the randomized grouping.

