### Study setting

The research objects will be recruited from the Seventh People’s Hospital affiliated to Shanghai University of Traditional Chinese Medicine, Shanghai Second Rehabilitation Hospital and Shanghai Hudong Hospital. Interventions for all patients will be conducted in hospitals where participants are recruited. The Seventh People’s Hospital affiliated to Shanghai University of Traditional Chinese Medicine will be responsible for trial coordination and data management.

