### Data analysis

#### Statistical analysis

Statistical analysis of research data will be performed by health statisticians and major researchers using SPSS or SAS. Pearson’s *χ*2 test or Fisher’s exact test will be used to analyze classified variables and continuous variables will be evaluated using Student’s *t* test or an appropriate non-parametric method. All statistical tests will be double-sided. The statistical significance level will be set at 5%. The measured data will be described by mean ± standard deviation. Before the analysis, the normality test and homogeneity test of variance will be carried out. If the normal distribution is satisfied, a *t* test will be used. The LSD or SNK method will be used for multiple comparisons, and the rank sum test will be used for non-normality or non-uniformity of variance.

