## Discussion

The timely relief of spasticity in stroke patients is particularly important for the rehabilitation of limb function, so it is a key step to apply effective treatment measures to relieve spasticity as much as possible. A preliminary clinical observation of 16 cases of hand spasm after stroke treated by fascial-point acupuncture has been completed in our group. The results show that fascial-point acupuncture can effectively alleviate hand spasm immediately after stroke. However, its cumulative effect, duration of spasm relief and long-term efficacy need further clinical study. Hence, here we propose a multicenter, prospective and randomized clinical trial to further evaluate the clinical efficacy of fascial-point acupuncture in relieving hand spasm after stroke.

In order to eliminate the interference of acupuncture itself on the experimental results, a sham acupuncture group will be established in this study. However, bias exists in all clinical trials. In our trial, the blindness of the acupuncturists and patients in designing a randomized controlled trial involving acupuncture manipulation will be the most challenging aspect. Therefore, surface EMG measurements are also used as part of the outcome assessment in addition to the scales used in previous studies. In recent years, EMG has been widely used in spasticity assessment, especially after stroke [26]. The application of electrophysiological measurement can provide quantitative information of spasticity and reduce the interference of subjective factors in scale evaluation. In addition, the multicenter development of the study is also related to biases, mainly including differences in acupuncture techniques. We tried to eliminate these biases by examining the needling procedures of other participating hospitals and training acupuncturists in all participating centers. We firmly believe that the results of this study will help to lay a foundation for the alleviation of hand spasm after stroke and functional improvement.

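### The named tests ignore hospital, although the article itself calls centre differences a source of bias; the cost is modest precision, and a hospital term recovers it

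*Protocol article*

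**What the plan says.** Study setting names three Shanghai hospitals and states: "Interventions for all patients will be conducted in hospitals where participants are recruited". So operators, case mix and routine rehabilitation can all differ by hospital.

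The Discussion accepts that this matters: "In addition, the multicenter development of the study is also related to biases, mainly including differences in acupuncture techniques". The measures offered are training of the acupuncturists and checking of their needling (Uniformity in acupuncture performance; Discussion).

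On allocation, Randomization says "Randomization will be accomplished by qualified researchers using randomization software to generate random-number sequences", sets a 1:1:1 ratio, and describes numbered opaque envelopes: "After obtaining informed consent, the envelopes will be opened in turn". It mentions neither hospital nor blocks. It also does not say that there is one shared series or that the sequence is unrestricted.

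On analysis, Statistical analysis names chi-square or Fisher for categorical variables, the t test for continuous ones, LSD or SNK for multiple comparisons, and a rank sum test as fallback. It adds "All statistical tests will be double-sided". Hospital does not appear.

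**The concern.** A source of variation that the plan itself names as a bias is absent from the analysis it specifies. Two things follow.

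- If allocation is not tied to hospital, one arm may by chance hold more patients from a hospital with milder spasm or better results. The named tests do not correct for that, and differences between hospitals stay in the error term.
- If allocation is balanced within hospitals, the design has already removed that variation from the treatment comparison, but an unadjusted test still counts it in the standard error. The test then rejects too rarely.

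In both cases hospital belongs in the comparison. At stake is precision, and a view of whether the effect of needling differs between hospitals.

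**Working it through.** **The plan's own size.** Sample size gives 63 per group, and 63/0.9 = 70 per group after losses, 210 in total. The 63 does not follow from the printed formula. Taking P as the mean of 50% and 85%, (1.65 + 1.28)² × 2 × 0.675 × 0.325 / 0.35² = 30.7, so 31. That is a separate matter; I use the planned 70 per arm.

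**Assumptions, not in the article.** Hospital sizes 110/60/40; a true difference of 0.5 SD between two arms; hospital means at 0, +d and −d, with d = 0.3 or 0.6 within-hospital SD.

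**Step 1: centre variance.** For d = 0.6 the weighted mean is 0.6 × (60 − 40)/210 = 0.057 and the mean square is 0.36 × 100/210 = 0.171. The variance is 0.171 − 0.003 = 0.168, a share of 0.168/1.168 = 14.4% of the total. For d = 0.3 the variance is 0.042, a share of 4.0%.

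**Step 2: approximate power, two-sided 5%, 70 per arm.** Power ≈ Φ(0.5 × √35 / s − 1.96), where s = 1 with hospital in the model and s = √(1 + centre variance) without it.

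- Hospital in the model: Φ(2.958 − 1.96) = 84.1%.
- Ignored, d = 0.3: Φ(2.898 − 1.96) = 82.6%.
- Ignored, d = 0.6: Φ(2.737 − 1.96) = 78.1%.

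**Step 3: alpha if lists are balanced per hospital but the test ignores hospital.** The effective critical value is 1.96 × s.

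- d = 0.3: 1.96 × 1.021 = 2.00, true alpha about 4.5%.
- d = 0.6: 1.96 × 1.081 = 2.12, true alpha about 3.4%.

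**Step 4: simulation with the same inputs.** At d = 0.6, power rose from 0.772 to 0.828 with unstratified lists, and from 0.787 to 0.842 with stratified lists. A repeat gave 0.78 rising to 0.82–0.83. At d = 0.3 the gain was about 1 point. With stratified lists and no adjustment, the null rejection rate at d = 0.6 was 0.036, and 0.033 on repeat. The hand calculation agrees to within about a point; it ignores the small losses from the t distribution and from unequal arms.

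**Step 5: binary outcome, assumed 70 per hospital and a 20-point effect, one unstratified list** (4,000 runs per cell).

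| Comparator rates by hospital | Power, unadjusted | Power, Mantel-Haenszel | Type I error, unadjusted |
|---|---|---|---|
| 50/50/50% | 0.670 | 0.670 | 0.054 |
| 40/50/60% | 0.662 | 0.674 | 0.056 |
| 30/50/70% | 0.678 | 0.723 | 0.050 |
| 20/50/75% | 0.688 | 0.784 | 0.048 |

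With stratified lists and no adjustment, type I error in the last row falls to 0.026.

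**Step 6: the plan's own effect.** Sample size states that P0 and P1 "represent the original curative effect and the expected curative effect, 50% and 85%, respectively". At 70 per arm, two-sided power is already 0.996 without centre effects. With hospitals of 110/60/40, simple randomization and logit shifts of 0/+1.1/−1.1, simulated power was 0.985 unadjusted and 0.989 with Mantel-Haenszel, a gain of 0.4 points.

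**The case against.** The strongest reply is that this is a condensed article. Blocking, strata and per-site envelope sets are commonly left to the full protocol, and covariate adjustment to the analysis plan; neither is shown. For allocation this stands. A reader might infer a single unrestricted sequence, and so badly unequal arms or large imbalances within hospitals. The article does not support that: it states neither a shared series nor unrestricted allocation, and the 1:1:1 ratio together with "and the sample size of each group is equal" under Sample size fits a restricted list at least as well. For analysis the reply stands only in part. An analysis plan could add hospital, but the article does name its tests, and they leave out a factor that its own Discussion treats as a source of bias.

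A reader might also infer systematic bias or a raised false-positive rate. Step 5 shows neither: without stratification, type I error stays at 0.048 to 0.056.

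Nor should rater differences between hospitals be counted as established. Outcome measures assigns evaluation to one blinded team member, although Data collection speaks of evaluators in the plural.

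Training and checking of needling are real mitigation of technique differences. They do not touch case mix, rehabilitation delivery or the error term.

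Finally, technique acts only in needled patients, so it is treatment-by-centre variation, which neither stratified lists nor a hospital main effect removes. That is correct, and it is why results by hospital are also needed.

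**Conclusion.** The point holds for the analysis: the tests as named leave out hospital, and including it is the better method whichever way the envelopes are organised. The size is modest. Under the assumed hospital sizes and 0.5 SD effect, adjustment is worth about 1 point of power at centre effects of 0.3 SD and about 5 points at 0.6 SD. In the binary example it ranges from nothing to about 10 points at the widest assumed spread. If lists are balanced per hospital, the unadjusted test runs at about 3% instead of 5% at 0.6 SD. At the protocol's own 50% versus 85% the loss is negligible, so the point matters mainly if the true effect is smaller than planned. Hospital sizes, centre effects and the smaller treatment effects are all assumptions, since the article gives none of them. No defect in allocation is shown; the article is simply silent on it.

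**What to change.** In Statistical analysis, include hospital in every efficacy comparison:

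- continuous outcomes: a linear model with arm and a fixed hospital term, with the pairwise arm comparisons taken from that model;
- binary outcomes: Mantel-Haenszel, stratified by hospital;
- if a rank test is kept: the van Elteren test in place of the plain rank sum test.

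Also show the acupuncture-versus-sham difference with its interval for each hospital, because a main effect does not capture technique differences. This display is descriptive: a hospital of 40 would have about 13 per arm, so the 95% interval would be roughly ±1.96 × √(2/13.3) = ±0.76 SD.

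The cost is 2 degrees of freedom. Hospital of recruitment is already known for every patient, and the change can be fixed before the database is locked.

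Secondary, and only if the full protocol does not already do so: keep a separate envelope series per hospital in permuted blocks of varying size, with the sizes unknown to recruiting staff. With an assumed 70 per hospital, blocks of 6 would bring the 95th percentile of the acupuncture-minus-sham count within a hospital down to 2, from 11 under one equal-arm list for all 210. Recruitment began on 1 June 2019, so a switch would mix two allocation schemes and would have to be documented. The analysis change carries most of the benefit without that.
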